### Withdrawals and Protocol Violations

All withdrawals and protocol violations will be recorded. As part of the trial information booklet and informed consent form, participants will be assured that they may withdraw their participation at any time without consequence or explanation. All participants who cease participation will be followed up to confirm their withdrawal. Participants will be given the option to comment on the reason for their withdrawal. If a participant does declare their reason for withdrawal, this will be recorded. Any alteration to the patient's health status or existing management regimens during the trial period will be recorded and factored into the final analysis and interpretation. This will include changes in medication/type of medication.

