### Inclusion Criteria

For inclusion, participants will have to meet several criteria: 18 years of age or over; and previous diagnosis of primary overt hypothyroidism by a qualified medical practitioner or specialist. If respondents are being medicated for their thyroid condition, it will be required that they be on a stable dose of medication for at least six months before entering the trial. Any alteration to a participant's medication levels during the trial will be recorded. Respondents who do not meet the inclusion criteria or who meet the exclusion criteria will be excluded from the study.

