### Statistical Analysis

Two-sample t-tests will be used to compare change from baseline for NET treatment versus control at each of six weeks and six months for the primary outcome measure. Linear mixed-effects models will be used examine change over time in the treatment and placebo groups for the basal temperature and basal heart rate groups as well as the other secondary outcome measures. A significance level of 5% will be used throughout the analysis. Because the analyses will be seen as hypothesis generating, no adjustment for multiple testing will be used. The R software program [39] will be used to conduct the analyses. Complete case analysis will be employed for participants who strictly followed the trial protocol. Sensitivity analysis will be used for withdrawals, missing data and participants who violate the study protocol eg. changes in medication during the study period. This will be done using imputation techniques including last value carried forward, and multiple imputation.

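### Changes in health status and medication after randomisation are allowed to shape the main NET-versus-placebo comparison, with no limit to supportive analyses

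*Protocol article*

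**What the plan says.** Three sections of the protocol article deal with changes during the trial.

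- **Inclusion Criteria** asks only for documentation: "Any alteration to a participant's medication levels during the trial will be recorded".
- **Withdrawals and Protocol Violations** goes further. It says that any change in a participant's "health status or existing management regimens during the trial period will be recorded and factored into the final analysis", and it names interpretation alongside analysis. It adds: "This will include changes in medication/type of medication". No covariate, exclusion, subgroup or sensitivity analysis is named.
- **Statistical Analysis** sets the primary test: "Two-sample t-tests will be used to compare change from baseline for NET treatment versus control at each of six weeks and six months". It then gives the analysis set: "Complete case analysis will be employed for participants who strictly followed the trial protocol". Everyone else is covered by: "Sensitivity analysis will be used for withdrawals, missing data and participants who violate the study protocol eg. changes in medication during the study period". The method is: "This will be done using imputation techniques including last value carried forward, and multiple imputation".

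**The concern.** The randomised comparison is protected only if nothing that happens after allocation decides who is analysed or what is adjusted for. Changes in health status and treatment can follow from allocation, and the document itself gives the routes:

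- Health status overlaps the outcomes, which are DASS depression and SF-36v2 functional health.
- Secondary Outcome Measures expects that thyroid hormone levels may move in unmedicated or under-treated participants during the trial.
- Adverse Reactions has the primary care provider told of significant changes in health status. That links a participant's course to later changes in management.

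If such changes enter the main comparison, through a model or through exclusions, the result need not be the effect of being assigned to NET or placebo. The open wording also leaves the choice of which changes count until after data are seen. Under Blinding, the chief investigator's concealment ends when a participant starts treatment, and that person also compiles and scores the DASS. The statisticians are blinded, which limits this risk but does not remove it.

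**Working it through.** **1. The plan's own figure.** Inputs from Power analysis and sample size justification: difference 4, SD 8, one-sided, 80% power, 51 per group. The 5% level is from Statistical Analysis. Normal approximation: n = 2 × (1.645 + 0.842)² × (8/4)² = 49.5, so 50 per group. The one-sided t-test gives 50.15, rounded up to 51, and power 0.806 at 51 per group. The stated size is reproduced. The point does not depend on it, but it supplies the 4-point scale used below.

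**2. The sections side by side.**

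| Change after randomisation | Withdrawals and Protocol Violations | Statistical Analysis |
|---|---|---|
| Medication | Enters final analysis and interpretation | Example of a violation, so outside the strict-adherence set and covered by sensitivity analyses |
| Health status, not a violation | Enters final analysis and interpretation | No handling stated |

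The primary t-test has no covariate term. Within that test, a change can affect the result only through who is included, and the strict-adherence restriction does exactly that for medication changers. The label of violation also sits oddly with Inclusion Criteria, which only records medication changes, and with Informed Consent, which asks nobody to alter existing treatment. These passages need to be reconciled.

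**3. Illustration for treatment changes triggered by worsening.** The document gives no rates, so everything here beyond the 4 points and SD 8 is assumed. Change score = −4 × (NET) + error with SD 8. The probability of a treatment change is 10% or 20% at a change score of zero, and its log-odds rise by 0.03, 0.06 or 0.12 per point of worsening. The treatment change itself lowers the score by 0, 2 or 4 points. Estimates are from 2,000,000 simulated participants:

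| Effect of the treatment change | All randomised | Adjusted for change | Changers excluded |
|---|---|---|---|
| None | −4.00 | −3.98 to −3.55 | −3.99 to −3.59 |
| 2 or 4 points | −3.98 to −3.73 | −3.98 to −3.55 | −3.98 to −3.58 |

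The largest shift is 4.00 − 3.55 = 0.45 points, with change rates of 16.9% on NET and 23.6% on placebo. The direction is not fixed. With a 4-point co-treatment effect, a 20% rate and log-odds 0.03, all randomised gives −3.92 and exclusion gives −3.96, slightly further from zero.

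**4. Illustration for a health-status score.** Suppose a score that NET shifts by 0.5 SD, with within-arm correlation r with DASS change, were used as a covariate. The adjusted effect is 4 − r × 8 × 0.5 = 4(1 − r). For r = 0.3, 0.5 and 0.7 this is 2.8, 2.0 and 1.2 points. The plan names no such score and no such model. This shows only why health status is the more sensitive variable.

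**5. Loss of numbers.** If 5%, 10%, 20% or 30% of each arm left the main set (assumed), 48, 45, 40 or 35 per arm would remain. One-sided t-test power would fall from 0.806 to 0.784, 0.761, 0.716 or 0.665, with the effect held at 4 points.

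**The case against.** The strongest reply is that the sentence covers interpretation as well as analysis and names no model, so a table by arm, a sensitivity analysis or a discussion could satisfy it. The named primary test is an unadjusted t-test. The Statistical Analysis section can be read as the way the general statement is carried out. The article is condensed, its analyses are described as exploratory, and the detail may sit in an analysis plan that is not shown.

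Much of this stands, and it rules out three stronger readings that a reader might infer.

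- *That the protocol prescribes adjustment for changes after randomisation.* It does not. The figures of 1.2 to 2.8 points therefore do not predict this trial's result.
- *That the two sections contradict each other outright.* They do not. For medication changes, one can implement the other. The mismatch is in scope and precision.
- *That the Statistical Analysis section keeps these changes safely in sensitivity analyses.* It does not. Its complete-case analysis is confined to strict adherers, so medication changers counted as violators are already outside it.

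The reply does not dispose of the point. Analysis is named separately from interpretation, so discussion alone does not clearly meet the sentence. The strict-adherence restriction is stated in the article, not left to another document. Calling the analyses exploratory does not make a comparison selected on later events a randomised one.

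**Conclusion.** The point holds as a rule that is fixed badly. One section commits changes after randomisation to the final analysis without limiting how. The other lets medication changes decide who is in the complete-case comparison and is silent on health-status changes that are not violations. The main comparison therefore need not estimate the randomised NET-versus-placebo effect.

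The size and direction of any bias cannot be derived from the document. For treatment changes triggered by worsening, the assumed scenarios give 0 to about 0.45 of 4 points. Adjustment for a health-status score close to the outcome could cost more, but that analysis is possible under the wording, not planned. The point should be corrected because the correction is cheap and the present wording leaves the main result open to choices made after the data are seen. It does not show that the trial's result will be wrong.

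**What to change.** Three linked edits are needed. Changing only the first section would leave the restriction in the second in force.

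1. In Withdrawals and Protocol Violations, replace the clause that brings alterations into the final analysis and interpretation with: *recorded with dates and summarised by arm*.
2. In Statistical Analysis, state that the primary comparison of DASS depression includes randomised participants regardless of later changes in health status or medication, and is not adjusted for, stratified by or restricted on them.
3. In the same section, label the strict-adherence analysis, and any other analysis that uses these changes, as supplementary. Such analyses remain allowed. They no longer supply the main result.

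The cost is a few sentences and one table by arm, with no more participants and no new outcome assessments. The downside is that differences between arms in co-treatment are described, not removed, and the primary estimate includes their effect.

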### Adverse Reactions

All adverse reactions will be recorded. In the published literature on NET there have been no documented adverse reactions [13,15-20]. It is not anticipated that participants will be exposed to any unnecessary risks. Due to the nature of the NET procedure/study protocol there is potential for a mild uncomfortable recall of past events in the NET treatment group. There is also potential for some mild focal soreness following the tapping procedures applied in both the NET and the placebo groups. Any participant experiencing anything more than a mild discomfort/soreness, or becoming emotionally distressed, will have their participation in the study reviewed and their potential for withdrawal assessed. In the case of any adverse reaction, the relevant help will be rendered to the participant at no charge. The primary health care provider will also be notified in the event of any significant changes/revelations in a participant's health status that are witnessed prior to commencement or during a participant's involvement in the trial.

### Randomisation and treatment allocation

Eligible participants will be randomly allocated to either the NET treatment group or the placebo (sham intervention) group. A random sequence generator will be used to produce a random sequence (1-200) with no repeats. These numbers will be recorded on individual pieces of paper and placed into envelopes which will then sealed and shuffled. After the participant has completed their initial blood test, the chief investigator will select an envelope for that participant. Participants allocated an even number will be assigned to the treatment group, and those receiving an odd number will be assigned to the placebo group.

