### Participants

Participants will respond via a toll-free number to advertisements placed in a variety of different media including; newspapers, magazines, websites, and flyers. An attempt will be made to disseminate hardcopy advertisements in a variety of geographical locations around Sydney. The advertisements will call for participation in a research project examining the influence of a new treatment for hypothyroidism (See Additional File 1). Respondents will be screened over the phone by the chief investigator to determine their eligibility to participate based on a set of inclusion and exclusion criteria. Eligible participants will then be sent a trial information booklet that explains the details of the trial. Participants will be given an opportunity to read through the trial information and make an informed choice as to whether or not they wish to participate in the research. One week after receiving the trial information booklet, potential participants will receive a follow-up telephone call from the chief investigator to ascertain their desire to participate, and to answer any further questions. From this point, willing participants will be sent the salient information to begin their involvement in the trial.

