### Blinding

The allocation of individual participants to treatment groups will be concealed to the chief investigator up until the point of a participant commencing treatment. Individual participants will not be told their group allocation until the completion of their involvement in the trial. All participants allocated to the placebo intervention group will have the opportunity to receive the NET treatment free of charge at the completion of their initial participation. No other incentives will be given for a participant's involvement or follow-up.

Any primary care providers (e.g. endocrinologist) will be blinded to the participant's group allocation. As the practitioners involved in the study will be performing both the NET treatment and the placebo intervention, it will be necessary for the group allocation to be disclosed to these practitioners. Practitioners will be instructed to perform the placebo with the same gusto as the NET treatment. The treating practitioners will have no previous role in the diagnosis or management of the participant's thyroid condition.

Group allocation will be concealed from the pathology company involved in the collection and analysis of the serum outcome measures. Statisticians involved in the analysis of the trial data will be blinded to group allocation.

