The DASS questionnaire will be issued to each participant at the specified times; study commencement, six-weeks and six-months. The results will be collected and forwarded to the chief investigator for compilation and scoring using relevant scoring algorithms and software [32].

Improvements in the negative emotional state of depression will be represented by decreased scores by respondents at 6 weeks and at 6 months. The associated anxiety and stress scores from the DASS will be included in the secondary outcome measures.

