### Secondary Outcome Measures

The secondary outcome measures (from serum analysis) are listed in Table 1. All blood collection and analysis will be performed by the commercial pathology laboratory DHM. The pathology company DHM provides pathology services to general practitioners, medical specialists, nursing homes, private hospitals and researchers [33].

**Table 1 T1:** Serum Secondary Outcome Measures

Test Name	Abbreviation	Reference Range
Thyroid Stimulating Hormone	TSH	0.40 - 4.00 mU/L
Free Thyroxine	FT4	9.0 - 19 pmol/L
Free Triiodothyronine	FT3	2.6 -6.0 pmol/L
Thyroglobulin auto-antibodies	Anti-Tg	0 - 80 IU/ml
Thyroid Peroxidase auto-antibodies	Anti-TPO	0 - 120 IU/L

Participants will be issued with a blood sample request form that can be used at any DHM collection centre. Blood samples will be obtained at the beginning of the trial, then again at the six week and six month points. Participants will be instructed to provide a blood sample that will be used to measure a variety of thyroid related indicators (See Table 1). There will be no specification regarding timing or fasting for the sample collection. The initial blood sample will completed one week prior to the first treatment in both groups. Blood samples will be spun in gel tubes at the collection centre before being couriered in cold storage to the central DHM laboratory for analysis. At the central laboratory, the ARCHITECT^® ^assay kits (Chemiluminescent Microparticle Immunoassay) will be used to measure the TSH, FT3, FT4 in the serum samples (Abbott Laboratories, Abbott Park, IL, USA). Immulite^® ^2500 will be used to quantify levels of anti-thyroid peroxidase antibodies and auto-antibodies to thyroglobulin in serum. The Immulite^® ^2500 method involves a solid-phase, enzyme labelled, chemiluminescent sequential immunometric assay (Siemens, Los Angeles, CA, USA). All results will be forwarded to the chief investigator for monitoring, compilation and analysis.

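### The chief investigator both recruits and draws envelopes that have no fixed order of use, and is unblinded while scoring the DASS and handling serum results

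*Protocol article*

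**What the plan says.** The protocol article gives the chief investigator a role at each of these stages.

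- **Eligibility (Participants):** "Respondents will be screened over the phone by the chief investigator to determine their eligibility".
- **Willingness (Participants):** "potential participants will receive a follow-up telephone call from the chief investigator to ascertain their desire to participate".
- **Sequence (Randomisation and treatment allocation):** "A random sequence generator will be used to produce a random sequence (1-200) with no repeats". Each number goes into its own envelope, and the envelopes are sealed and shuffled. Even numbers mean NET and odd numbers mean placebo.
- **Draw (same section):** after the initial blood test, "the chief investigator will select an envelope for that participant". Secondary Outcome Measures places that blood test one week before the first treatment.
- **End of concealment (Blinding):** "The allocation of individual participants to treatment groups will be concealed to the chief investigator up until the point of a participant commencing treatment".
- **Primary outcome handling (Primary Outcome Measures):** "The results will be collected and forwarded to the chief investigator for compilation and scoring", with scoring algorithms and software.
- **Serum outcome handling (Secondary Outcome Measures):** "All results will be forwarded to the chief investigator for monitoring, compilation and analysis".
- **Blinded analysis (Blinding):** "Statisticians involved in the analysis of the trial data will be blinded to group allocation".

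**The concern.** There are two separate problems, and they should be kept apart.

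The first is at entry. The person who judges eligibility and speaks to each candidate also chooses which envelope that candidate receives. With a numbered series used strictly in order, a departure leaves a gap. With a shuffled set from which one envelope is picked, it does not. Protection against selection then rests on one person's conduct and not on the procedure.

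The second comes after entry. From the start of treatment the chief investigator may know the arm, and every six-week and six-month outcome arrives after that point. Compilation, scoring and the analysis of serum results can then be done with knowledge of the arm, while the article tells the reader that the statisticians are blinded. A reader could take the whole outcome path to be blinded, and the text does not secure that.

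**Working it through.** No figure in the article sizes this point, so the check sets the sections side by side.

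**1. Entry.** Participants gives screening and the willingness call to the chief investigator, and Randomisation and treatment allocation gives the same person the draw. The steps described for the envelopes are sealing, shuffling and selecting. The set holds 200 envelopes for a planned minimum of 102 participants, so 200 − 102 = 98 are surplus at that size. With a surplus and no order of use, one envelope opened and laid aside leaves no visible gap. A count of opened and still-sealed envelopes against the 200 could expose a discarded one, but no count is described.

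**2. Draw against concealment.** The draw follows the initial blood test, which is a week before first treatment. Blinding says the allocation stays hidden from the chief investigator until treatment starts. Both can be true only if the chief investigator picks the envelope without opening it or learning its content. The text does not say who opens it.

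**3. After entry.** Outcomes are collected at baseline, six weeks and six months. The chief investigator's concealment ends at treatment start, so both post-baseline collections fall after it.

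| Task | Who | Protected by blinding after treatment starts? |
|---|---|---|
| DASS compilation and scoring | Chief investigator | No |
| Serum monitoring, compilation, analysis | Chief investigator | No |
| Statistical analysis by statisticians | Statisticians | Yes |
| Deciding who adhered to the protocol | Not named | Not stated |

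The last row matters because Statistical Analysis restricts the complete-case analysis to strict adherers. Withdrawals and Protocol Violations adds that changes in health or treatment enter the analysis and interpretation.

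**4. Scale, by assumption only.** Suppose a fraction f of allocations were steered, and the participants steered to the two arms differed by g points in expected DASS change. The between-arm difference would shift by about f × g:

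- f = 0.05: 0.05 × 4 = 0.2 to 0.05 × 8 = 0.4 points
- f = 0.10: 0.10 × 4 = 0.4 to 0.10 × 8 = 0.8 points
- f = 0.20: 0.20 × 4 = 0.8 to 0.20 × 8 = 1.6 points

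The target difference in the power statement is 4 points. Neither f nor g comes from the article, and nothing in it suggests that steering occurs. The range only shows that the answer depends wholly on unknown inputs.

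**The case against.** The case for the plan has real force.

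- **A sealed, shuffled set is not predictable.** The draw comes after screening, the information booklet, the follow-up call and the blood test. The allocation is stated to be hidden from the chief investigator until treatment starts. This stands: what remains is a deliberate redraw, not foreknowledge.
- **Learning the arm later cannot undo concealment at entry.** This also stands. It bears on blinded data handling only.
- **The DASS leaves a scorer little room.** It is self-reported by participants who are not told their arm, and the depression score is a sum of 14 items rated 0 to 3, computed by algorithm. This stands and limits the harm for the primary outcome.
- **An article may leave envelope detail to the full protocol.** This stands for opacity, outer numbering and a log. A reader might infer that the envelopes are unnumbered, but the text is silent on that. What the article does state, shuffling followed by selection by the recruiter, is enough for the point.

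Three stronger readings are tempting but not supported.

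- **That the sections contradict each other on blinded analysis.** The promise covers statisticians only and can hold while the chief investigator also analyses. The sentence giving analysis to the chief investigator closes the paragraph on blood samples, so it supports analysis of serum results and not of the DASS.
- **That the chief investigator decides who adhered to the protocol.** No one is named for that task.
- **That the draw fails to deliver the planned 51 per group.** The 51 is a power figure, and the sample is stated as at least 102. If 102 of 200 envelopes are drawn (100 odd, 100 even), the SD of an arm's size is √(102 × 0.5 × 0.5 × 98/199) = 3.5, with a 95% range of 44 to 58. One-sided t-test power for 4 points with SD 8 is 0.806 at 51:51 and 0.799 at 44:58. The loss is immaterial.

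**Conclusion.** The point holds in two parts. As described, recruitment and the envelope draw lie with one person and there is no fixed order of use, so a set-aside or redrawn envelope would not be detectable. Separately, the chief investigator scores the DASS and handles and analyses serum results after concealment from that person has ended. This is in tension with the blinded-statistician statement, and the two places should be reconciled.

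The size of any bias cannot be derived from the document. For the DASS it is limited by self-report and algorithmic scoring. The conclusion assumes that the article's sequence of steps is the one actually used, and that the full protocol adds no independent allocator or log. It implies nothing about anyone's conduct. The design should be changed where that is still possible, but the defect does not by itself invalidate the trial.

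**What to change.** 1. **Remaining allocations.** Have an existing co-investigator without participant contact hold sequentially numbered, opaque, sealed envelopes. Assign them strictly in order against a dated log, and have the treating practitioner open them.
2. **Blinding section.** Extend the chief investigator's blinding to database lock where feasible. Failing that, have data compiled and scored under A/B codes. Fix protocol-adherence and analysis-set decisions before the code is broken.
3. **Secondary Outcome Measures.** Reword the sentence on serum results so that analysis is done by the blinded statistician.

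**Cost.** This needs a small task for a co-investigator and revised wording. Informed Consent mentions supervisors and co-investigators, but whether one of them has no participant contact is an assumption. Practitioners may reach the chief investigator at any time. Participants also learn their arm on finishing, and placebo participants are then offered NET. Queries and disclosures that reveal the arm would therefore have to go to the co-investigator.

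**Timing.** Recruitment was to run from September 2006 to March 2010, and the article cites a 2009 publication, so item 1 may reach few or no participants. Items 2 and 3 remain usable up to the analysis.

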### Informed Consent

In addition to the trial information booklet, all participants will be issued with a copy of the informed consent form. The consent form will detail the names of the individuals involved with the study: chief investigator; supervisors/co-investigators; practitioners. Participants will also be informed that the research is being conducted by the Department of Chiropractic at Macquarie University. A brief description of the study protocols will also provided; duration of the study; outcome measures employed; adverse reactions to treatment and the associated back-up counselling services; ethics approval and contact details of the ethics officer; the right to cease participation at any time; methods for dissemination of results; complaint procedures and privacy policy. Participants will not be asked to alter or cease any existing treatment regimens. Any concurrent treatment regimens will be recorded.

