### Sample

The study population will consist of at least 102 individuals with a diagnosis of overt primary hypothyroidism, who are undergoing a variety of management strategies (including no treatment), from Sydney, Australia. A justification for the sample size is provided later.

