It is anticipated that the majority of participants will be receiving treatment in the form of L-Thyroxine supplementation. For this reason, serum measures of TSH, serum FT4, serum FT3 should fall within normal reference ranges (See Table 1) provided there are no major alterations to this existing treatment strategy. In adequately treated participants, the addition of the experimental intervention should not influence serum thyroid hormone levels. However, in individuals who are not being medicated, or in individuals who are being under-treated upon entry into the trial, a decrease in TSH measurements and an increase in FT4 and FT3 measurements may be expected during the course of the trial.

In individuals who are being over-treated, elevated FT4 and FT3 levels and decreased TSH measurements will be demonstrated at baseline. It is expected that there will be no change in the serum measures in this subgroup.

It is unclear how the autoimmune markers will respond to the addition of NET to any existing treatment regimens.

In addition to the serum measures, participants will fill out the SF-36v2 and the additional items (anxiety and stress) of the DASS.

The SF-36v2 health survey is a questionnaire used to assess outcomes in eight different domains: role limitations because of physical or emotional problems, physical and social functioning, bodily pain, perception of mental and general health, and vitality [34].

Improvements in functional health and well-being as measured by the SF-36v2 will be depicted by increased scores by the respondents at six weeks and at six months. Deterioration in functional health and well-being will be revealed by a decrease in SF-36v2 scores.

Two additional secondary outcome measures are to be completed and recorded by participants at home for each day of the six month trial period are listed below:

Basal Heart Rate (BHR)

Basal Temperature (BT)

After signing up to take part in the trial, participants will be given a home diary, digital thermometer and instructions on how to record their BHR and BT. Participants will be instructed to make an effort to perform these measurements at the same time each day, and ideally before getting out of bed in the morning. For BHR measurements, participants will be instructed to find their radial pulse and then record the number of beats that occur in one minute and record this figure in the diary provided.

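### The primary t-test on change in DASS depression uses neither baseline DASS nor entry thyroid status as a covariate, and so gives up precision that data already collected would provide

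*Protocol article*

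**What the plan says.** - **Population.** The Sample section admits people "who are undergoing a variety of management strategies (including no treatment"). Secondary Outcome Measures expects most to be on L-thyroxine but gives no proportion.
- **Allocation.** Randomisation and treatment allocation describes one pool: "A random sequence generator will be used to produce a random sequence (1-200) with no repeats". The rule is then: "Participants allocated an even number will be assigned to the treatment group". Odd numbers go to placebo. No stratum is named. The envelope is chosen after the initial blood test.
- **Primary analysis.** For DASS depression, Statistical Analysis states: "Two-sample t-tests will be used to compare change from baseline for NET treatment versus control at each of six weeks and six months". A two-sample t-test has no place for a covariate, so this is a stated choice and not a detail left open.
- **Secondary analysis.** "Linear mixed-effects models will be used examine change over time in the treatment and placebo groups". No covariates are listed.
- **Data available.** DASS and serum measures are taken before the intervention (Measures). Under Informed Consent, "Any concurrent treatment regimens will be recorded".
- **Predicted role of thyroid status.** Secondary Outcome Measures expects, "in individuals who are not being medicated, or in individuals who are being under-treated upon entry into the trial, a decrease in TSH measurements". FT4 and FT3 are expected to rise in the same people. It expects no serum change in adequately treated or over-treated participants, and it makes a similar split for basal temperature. It says nothing of the kind about depression.

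**The concern.** Two things are lost when a continuous outcome with a recorded baseline is analysed by an unadjusted test on change.

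First, the change score subtracts the whole baseline value. Unless baseline and follow-up are almost perfectly correlated, that over-corrects and leaves avoidable noise in the comparison.

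Second, with unstratified allocation of about 102 people, the arms can differ by chance in baseline DASS or in the share who are un- or under-treated. The t-test leaves the effect of that difference in the estimate. Its standard error allows for this on average over repeated randomisations, but the single estimate that is reported still carries it.

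The trial is powered at 80% with a one-sided calculation and has little margin, so free precision is worth taking.

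**Working it through.** **Inputs.** From Power analysis and sample size justification: difference 4 points, SD 8, 51 per arm, one-sided, 80% power. From Statistical Analysis: 5% significance level. Assumed, because the protocol gives none of them: the baseline-to-follow-up correlation r = 0.4 to 0.7, with equal SDs at both times; 10 to 20 of 102 participants un- or under-treated; a gap of g = 2 to 6 DASS points in mean change between the status groups.

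**1. The plan's own figure.** SE = 8 × √(2/51) = 1.58. One-sided power = Φ(4/1.58 − 1.645) = 81.1%. The t-based solution is 50.15 per arm, which rounds up to the stated 51. The figure reproduces.

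**2. Adjusting for baseline DASS.** With raw SD σ, the change score has variance 2σ²(1 − r) and ANCOVA has residual variance σ²(1 − r²). The ratio is (1 + r)/2. Taking 8 as the SD of change:

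| r | Variance ratio | Effective SD | One-sided power | Two-sided power |
|---|---|---|---|---|
| change score | 1 | 8.00 | 81.1% | 71.4% |
| 0.4 | 0.70 | 6.69 | 91.5% | 85.5% |
| 0.5 | 0.75 | 6.93 | 89.8% | 83.0% |
| 0.7 | 0.85 | 7.38 | 86.3% | 78.2% |

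The protocol does not say whether 8 is the SD of change or of the score. If it is the SD of the score, the variance ratio is the same but the starting point moves. At r = 0.4 the SD of change is 8√1.2 = 8.76, and power goes from 74.5% to 86.7% (SD 8√0.84 = 7.33). At r = 0.7 the SD of change is 8√0.6 = 6.20, and power goes from 94.7% to 97.1% (SD 8√0.51 = 5.71). ANCOVA gains in every case.

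**3. Baseline imbalance.** Given a chance difference d between arms at baseline, the expected difference in change shifts by −(1 − r)d. That is 0.3 to 0.6 points per point of imbalance for r = 0.7 to 0.4. ANCOVA removes this shift.

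**4. Adding thyroid status.** Share of variance explained R² = p(1 − p)g²/64.
- Low end, p = 10/102 and g = 2: R² = 0.0055, SD 7.98, power 81.2%.
- High end, p = 20/102 and g = 6: R² = 0.089, SD 7.64, power 84.1%.

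So status alone explains about 0.6 to 9% of variance and is worth about 0 to 3 points of power.

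**5. Chance imbalance in status.** With 20 un- or under-treated participants, drawing without replacement from 100 even and 100 odd envelopes gives a split of 13:7 or worse with probability 24%, and 14:6 or worse with probability 10%. With arms fixed at 51 each, these are 21% and 8%. A 14:6 split is a difference in share of 8/51 = 0.157. It moves the unadjusted DASS difference by 0.31 points (g = 2) to 0.94 points (g = 6), at most 0.6 of the standard error of 1.58.

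**The case against.** Simple randomisation with an unadjusted test is a legitimate choice in a pilot whose analyses are declared hypothesis-generating. The t-test keeps its type I error, and chance imbalance is already allowed for in its standard error. All of that stands, and it is why this is an improvement and not an error.

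Three stronger readings are tempting, and the protocol does not support them.

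- **Thyroid status decides who can respond on the primary outcome.** The predictions by status concern serum hormones and basal temperature. Depression was chosen precisely because managed patients stay symptomatic (Primary Outcome Measures). The Background links severe hypothyroidism to the presence of depression, not to change in it.
- **The whole analysis ignores status.** This is shown only for the primary t-test. Covariates for the mixed models may be listed in a document not at hand. Changes in medication during the trial are to be recorded, factored into the analysis and covered by sensitivity analysis, although that does not cover status at entry.
- **Status is strongly prognostic for DASS.** A share of 5 to 15% of variance would mostly need larger gaps than the 2 to 6 points assumed here. With 20 affected, 15% needs a gap of about 7.8 points, nearly twice the target effect.

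It is also fair to say that a main-effect covariate does not address effect modification, which is what the serum and temperature predictions describe.

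**Conclusion.** The point holds as a low-cost improvement to the primary analysis. The planned test is valid but inefficient. Nearly all the gain comes from baseline DASS: variance falls to about 0.70 to 0.85 of that of the change score, and one-sided power is about 86 to 92% against 81%, assuming r between 0.4 and 0.7 and an SD of change of 8. Entry thyroid status contributes little for DASS, about 0 to 3 points of power under the assumed prevalence and gap. Its use there is mainly to take out any visible imbalance. For serum hormones and basal temperature, status matters by the protocol's own account, but as a modifier of the treatment effect.

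**What to change.** In Statistical Analysis, replace the two-sample t-tests for the primary outcome with a linear model (ANCOVA) of the DASS depression score, fitted at six weeks and at six months, with these terms:

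- treatment arm;
- baseline DASS depression;
- entry thyroid status: unmedicated, or medicated with baseline TSH above, within or below the Table 1 range, with a rule written in advance for merging sparse levels.

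The arm coefficient, with its confidence interval, is the primary estimate. The unadjusted t-test can stay as a supporting analysis.

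For serum hormones and basal temperature, state in the mixed models an arm-by-status term (with time, where change over time is modelled), so that the predicted difference in response is tested directly.

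The cost is one degree of freedom for baseline DASS and one to three for status, out of 100 (102 − 2), and no new data, visits or participants. The wording should be fixed before the group codes are released. No change to the envelopes is needed; recruitment was in any case due to end in March 2010.
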